#### Secondary outcomes

Secondary outcomes will be assessed at all measurement points (baseline, post-intervention 10 weeks after randomisation, and follow-up 6 months after randomisation).

Fatigue severity will be measured using the Fatigue Severity Scale (FSS; [40]), comprised of nine items, each rated on a 7-point Likert scale ranging from 1 to 7. The total score ranges from 9 to 63. Internal consistency is good, with *α* = 0.88 [40].

Depression-related symptom severity will be measured using the 9-item version of the Patient Health Questionnaire (PHQ-9; [41]), with response options ranging from 0 to 3, a total score from 0 to 27, and a good *α* of 0.89.

Health-related quality of life will be assessed using the Assessment of Quality of Life (AQoL-6D; [42]), a questionnaire comprised of 20 items that measure six domains (independent living, pain, senses, mental health, coping, relationships). A total score can be calculated across all domains, ranging from 20 to 99. The domains’ reliability ranges from *α* = 0.50 (senses) to *α* = 0.86 (independent living; [42]). Patients’ health (range 0 to 100) will be measured using the slider bar item of the European Quality of Life 5 Dimensions 5 Level questionnaire (EQ-5D-5L [43]).

Daylight exposure will be assessed with a self-developed 5-item questionnaire adapted from the item on daylight exposure of the Munich Chronotype Questionnaire [44]. These five items assess how much time patients have been spending in daylight, on average, at five different time periods during the day (in the early morning (before 8.00 a.m.), later morning (8.00–11.59 a.m.), noon (12.00 p.m. to 2.59 p.m.), afternoon (3.00 p.m. to 5.59 p.m.), evening (6.00 p.m. and after)) over the past 7 days. Total time spent in daylight will also be calculated (see Appendix 1 for further details).

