Patients’ physical activity level (i.e., time spent in vigorous- and moderate-intensity activity, walking, and sedentary activity) will be measured using the International Physical Activity Questionnaire – Short Form (IPAQ-SF; [45]). The IPAQ-SF is comprised of seven items that ask individuals to indicate both the number of days and average time over the past week that they have spent at each activity level. A total physical activity level will be estimated by weighting the reported minutes per week within each activity category by a metabolic equivalent (MET) energy expenditure estimate assigned to each activity category (e.g. cycling at vigorous intensity = 8, walking at moderate intensity = 3.3, sitting = 1; see [45]). The weighted MET-minutes per week will be calculated as duration × frequency per week × MET intensity. Test–retest reliability has been found to be very good, with Spearman’s *ρ* = 0.80 [45].

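### As written, the total physical activity score counts sitting at 1 MET, so extra sitting raises it when active minutes are unchanged

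*Protocol article*

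**What the plan says.** The physical activity paragraph under Secondary outcomes in the protocol article makes three statements that belong together.

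- The activity level covers four kinds of time: "time spent in vigorous- and moderate-intensity activity, walking, and sedentary activity".
- The total is built across these categories: "A total physical activity level will be estimated by weighting the reported minutes per week within each activity category". Each category has its own MET value, and the examples given are "cycling at vigorous intensity = 8, walking at moderate intensity = 3.3, sitting = 1".
- The formula is stated: "The weighted MET-minutes per week will be calculated as duration × frequency per week × MET intensity".

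The paragraph does not exclude sitting from the total, reverse its sign, or set it aside as a separate variable. Physical activity is a secondary outcome measured at baseline, 10 weeks and 6 months. Under Statistical methods {20a}, secondary endpoints are to be analysed much as the primary outcome is, with 95% confidence intervals for treatment effects.

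**The concern.** A positive weight on sitting matters only if sitting minutes enter the weighted sum. Read plainly, the rule therefore adds sedentary time to a score labelled as physical activity. Minutes sitting can far outnumber minutes in the active categories, so even a weight of 1 can contribute a large part of the total.

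Two consequences follow. First, patients can be ranked wrongly: one who does nothing but sit for longer can score above one who exercises. Second, a change in sitting with no change in activity shows up as a change in activity.

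The second consequence is relevant in this trial because both arms include sleep restriction with an agreed bedtime window (Intervention description {11a} and Table 1). Less time in bed means more time awake. Any of that time spent sitting would raise the score although the patient is no more active. If the arms differed in how well patients kept to the bedtime window, part of that difference could appear as a difference in physical activity.

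**Working it through.** The article gives no numerical total for this outcome, so there is no figure to reproduce. The check applies the stated rule with and without the sitting term.

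**Inputs.** The weights are the article's: vigorous (cycling) 8, walking 3.3, sitting 1. The general weight for moderate activity is not given, so the profiles contain no moderate activity other than walking. All patient profiles are assumptions made for illustration.

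**Formula.** Total = Σ (minutes per day × days per week × MET).

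**Step 1: one extra hour of sitting per day, all else unchanged.** 60 × 7 × 1 = 420 MET-min/week. This equals 420 / 3.3 ≈ 127 min/week of walking, or 420 / 8 = 52.5 min/week of vigorous activity.

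**Step 2: assumed profiles.**

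| Profile (per week) | Active part | Sitting part | Total as written | Sitting share | Total without sitting |
|---|---|---|---|---|---|
| A: walking 150 min; sits 4 h/day | 150 × 3.3 = 495 | 4 × 60 × 7 = 1680 | 2175 | 77% | 495 |
| B: walking 150 min; sits 8 h/day | 495 | 8 × 60 × 7 = 3360 | 3855 | 87% | 495 |
| C: no activity; sits 10 h/day | 0 | 10 × 60 × 7 = 4200 | 4200 | 100% | 0 |
| D: walking 420 min, vigorous 90 min; sits 4 h/day | 420 × 3.3 + 90 × 8 = 1386 + 720 = 2106 | 1680 | 3786 | 44% | 2106 |

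A and B are equally active but differ by 1680 under the rule as written. C, with no activity at all, scores above D. Without the sitting term, A and B tie, D ranks highest and C scores zero.

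**Step 3: activity replacing sitting.**

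- 60 min of sitting becomes walking: 60 × (3.3 − 1) = 138, against 60 × 3.3 = 198 without the sitting term. The loss is 60 / 198 ≈ 30%.
- 60 min of sitting becomes vigorous activity: 60 × (8 − 1) = 420, against 60 × 8 = 480. The loss is 60 / 480 = 12.5%.

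The sign is right in both cases. Conversely, if 60 min of walking gives way to sitting, the total falls by 138. The score therefore rises with sitting only when active minutes are unchanged, that is, when the added sitting replaces time the questionnaire does not count, such as time in bed.

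**The case against.** The strongest defence is that the article never says outright that sitting is summed. The weight for sitting stands in a list of examples that ends by pointing to the cited questionnaire source, and detailed scoring is often left to the SAP. The full documents may well keep sitting apart. That stands as a reason not to claim that the trial will in fact score it this way. It does not rescue the text, because the article states categories, weights and a formula, and together they include sitting. This is a stated rule, not missing detail.

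It is also fair to say that the harm is limited. The outcome is secondary, and the category times are collected, so the total can be recomputed.

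A reader might infer three stronger claims, none of which the article supports.

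- *That the outcome would not measure activity.* Step 3 shows that replacing sitting with activity still raises the score.
- *That arm differences would mostly reflect noise in reported sitting.* The article gives no variance or reliability for sitting time. A large share of one patient's total says nothing about the share of the variance or of the arm contrast. Noise equal in both arms would cost precision and would not by itself create a difference.
- *That the layout of the seven items proves the formula cannot apply to sitting.* The article does not set out which item asks what. A daily sitting time would fit the formula with a frequency of 7.

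**Conclusion.** The point holds in a limited form. On its plain reading, the published rule adds sitting to total physical activity at 1 MET per minute. With active minutes unchanged, that is 420 MET-min/week for each extra hour of sitting per day, enough to place an inactive patient (4200) above an active one (3786) in the assumed profiles. Gains from replacing sitting are understated by about 30% for walking and 12.5% for vigorous activity, with the direction preserved.

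The weights are the article's and the profiles are assumed, so the sitting shares of 44% to 100% are illustrations, not estimates for this population. Whether the arms would be affected differently cannot be judged from the article. The primary ISI non-inferiority test, the sample size and the subsequent superiority test do not use this score. The rule should be changed, but it does not threaten the main conclusion.

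**What to change.** Define total physical activity as the sum of vigorous, moderate and walking MET-minutes per week. Remove the weight of 1 for sitting from that total, and report sitting time as a separate variable. If the full protocol or SAP already scores it this way, correct the published text to match. The cost is one line of text and, if needed, a small change in the scoring code. No new data are required.

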#### Health-economic evaluation

Quality-adjusted life years (QALYs) will be based on the AQoL-6D, which generates patient preference-based utilities on a scale of 0 (death) to 1 (perfect health), using the time-trade-off method [46]. QALY gains will be estimated by calculating the area under the curve (AUC) of linearly interpolated AQoL-6D utilities between measurement points to cover the follow-up period. Healthcare use, patient and family expenditures, and productivity losses will be self-assessed with the Trimbos and Institute for Medical Technology Assessment “Treatment Inventory of Costs in Patients with psychiatric disorders” questionnaire (TiC-P) and used for costing from a societal and public healthcare perspective.

For the health-economic evaluation, direct medical costs and costs due to absence from work or reduced efficiency during paid or unpaid work will be assessed at baseline and follow-up using the TiC-P [47, 48]. A list of unit cost prices will be utilised to compute healthcare costs on a per-participant basis [49]. The questionnaire’s test–retest reliability has been shown to be acceptable [48]. Budget impact will be presented as a difference in costs, with a comparison of various uptake levels of therapist-guided iCBT-I across different scenarios, estimating the expected change in healthcare system expenditures after different uptake levels of therapist-guided iCBT-I. The costs of healthcare of various intervention mixes (therapist-guided iCBT-I and face-to-face CBT-I) are compared with the *status quo*.

#### Descriptive and exploratory outcomes

Descriptive and exploratory outcomes will be assessed at baseline and post-intervention, unless otherwise stated.

Perceived benefits and disadvantages of online therapy will be assessed using a 29-item self-developed questionnaire (called the Patient Acceptance and Convenience Inventory). Twenty-seven of these items are answered on a 4-point Likert scale (ranging from 1 to 4 with a total score ranging from 27 to 108) and two are open-ended questions (see Appendix 1 for details). At post-intervention, session attendance will be assessed with one item and adherence to CBT-I methods with nine self-developed items, each rated on a 5-point Likert scale with response options ranging from 1 to 5 and a total score ranging from 9 to 45 (see Appendix 1 for details).

Attitudes towards internet-delivered psychotherapy will be measured employing the subscale “Relative advantage” of the E-Therapy Attitude Measure (ETAM; [31]), consisting of six items, with response options ranging from 1 to 5, a total score from 6 to 30, and excellent internal consistency, with *α* = 0.92.

Attitudes towards internet-delivered as well as face-to-face psychotherapy will additionally be assessed using the “Attitudes” subscales of the e-Therapy Attitudes and Process Questionnaire (eTAP; [50]) and Therapy Attitudes and Process Questionnaire (TAP; [51]). Both subscales have four items, each rated on a 7-point Likert scale (1–7) resulting in total scores ranging from 4 to 28. Internal consistency for these two subscales has been reported to be excellent, with *α* values of 0.92 (eTAP) and 0.91 (TAP), respectively.

Patients’ preference for the therapy format (one item with three response options), how well they can imagine engaging in the therapist-guided iCBT-I as well as face-to-face delivered CBT-I (two items, each rated on a 4-point Likert scale) and most important reasons for or against therapist-guided iCBT-I (two open-ended questions) will be measured using five self-developed items (see Appendix 1 for details).

User experience of the therapist-guided iCBT-I will be measured at post-intervention (only for the iCBT-I group) using the Short Version of the User Experience Questionnaire (UEQ-S; [52]). For this, the reported internal consistencies are good (subscales: Pragmatic Quality: *α* = 0.85; Hedonic Quality: *α* = 0.81).

All self-developed questionnaires (German and English translation) can be found in the Appendices in Additional File 1.

#### Safety

Adverse events related to treatment will be assessed at baseline and post-intervention in two ways. First, the occurrence and impact of possible negative effects during treatment will be measured using the 20-item Negative Effects Questionnaire (NEQ; [53]). The NEQ’s total scores range from 0 to 20 for the occurrence and 0 to 80 for the impact of negative effects. The questionnaire’s internal consistency has been reported to be *α* = 0.95. Second, a self-developed 24-item questionnaire on adverse effects commonly observed during CBT-I will be used (Simon L, Rozental A, [name], et al: The Negative Effect Questionnaire - Insomnia - An amendment of the Negative Effect Questionnaire for the treatment of insomnia, in preparation).

Furthermore, adverse events related to treatment (e.g. fatigue, sleepiness) will be assessed continuously during treatment. In the therapist-guided iCBT-I group, patients will be asked to report adverse events in sessions 2 through 6. During face-to-face CBT-I, therapists will ask for adverse events and record them in a designated electronic case report form (eCRF). Also, concomitant medication will be recorded in sessions 4 and 6 in both conditions (see Appendix 1 for details).

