**Methods:**

This study protocol describes a randomised controlled two-arm parallel-group non-inferiority trial comparing therapist-guided iCBT-I with face-to-face CBT-I in routine clinical care. A total of 422 patients with insomnia disorder will be randomised and treated at 16 study centres throughout Germany. Outcomes will be assessed at baseline, 10 weeks after randomisation (post), and 6 months after randomisation (follow-up). The primary outcome is insomnia severity measured using the Insomnia Severity Index. Secondary outcomes include depression-related symptoms, quality of life, fatigue, physical activity, daylight exposure, adverse events related to treatment, and a health-economic evaluation. Finally, potential moderator variables and several descriptive and exploratory outcomes will be assessed (e.g. benefits and disadvantages of internet-delivered treatment).

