The therapist-guided iCBT-I will be delivered via an access-controlled online platform [34] designed as an interactive website that includes video clips, written information, graphical illustrations, written and audio exercises, examples of other (fictional) patients, and an app-based sleep diary. It is a revised version of an intervention initially developed for workers suffering from insomnia, which we adapted to the routine care setting. The original intervention has been positively evaluated in three randomised controlled trials [35–37]. Therapists have access to their patients’ data and provide written feedback after each completed session (e.g. validating exercises patients completed within the sessions, motivating patients to implement exercises, like sleep restriction therapy, in their daily lives and/or providing additional information). Therapists are advised to provide feedback within two working days and to spend no more than 60 min for writing their feedback for one session.

In the face-to-face CBT-I condition, therapists and patients together work out the CBT-I components. For example, therapists provide information (e.g. psychoeducation about sleep and insomnia) and introduce exercises (e.g. sleep restriction therapy) that patients will be asked to implement in their daily lives. Psychoeducational elements, therapy exercises, and media (e.g. audio relaxation exercises) are the same as those used with the iCBT-I. Patients receive a paper and pencil sleep diary, which is commonly used in routine care CBT-I.

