Third, one previous study found that patients preferred face-to-face CBT-I before receiving this treatment, and patients receiving face-to-face CBT-I were more satisfied afterwards than patients receiving therapist-guided iCBT-I [24]. The present study will contribute to these findings by evaluating patients’ attitudes towards internet-delivered and face-to-face treatment, including treatment preferences, expectations, and acceptance, including the perceived convenience of each treatment format. Furthermore, these characteristics will be assessed before and after treatment to explore whether personal experiences with the respective therapy alter patients’ attitudes and expectations. In addition, advocates of internet-delivered therapy regularly highlight potential benefits, such as time and location independence or anonymous usability [18]. However, for CBT-I, it is largely unknown whether these advantages are actually experienced by patients. The comprehensive assessment of potential benefits will provide insights from a patient’s perspective.

Fourth, practitioners might hesitate to recommend digital therapy due to patient safety concerns. As prior trials focused on desirable outcomes, these concerns were only considered in a few studies [23, 26]. The present study will systematically investigate negative side effects and adverse events post-treatment as well as throughout treatment, thereby providing more data on the safety of therapist-guided iCBT-I.

Fifth, health-economic evaluations are particularly important for policymakers to have evidence for the best possible allocation of limited resources within the healthcare system [64]. While prior health-economic evaluations of therapist-guided iCBT-I (e.g. [47]) have demonstrated cost-effectiveness when compared to patients being on a waiting list, the present study will provide data for two effective treatments for the first time.

Finally, most participating centres are specialised in sleep medicine and provide CBT-I in routine care. Therefore, the current study serves as a template on how to integrate internet-delivered CBT-I into routine care processes, thereby facilitating later implementation.

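### Adverse events during treatment are collected differently in the two arms, so for this in-session stream a between-arm difference cannot be separated from the collection method

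*Protocol article*

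**What the plan says.** The Safety section describes two streams of harms data.

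**Questionnaires at baseline and post-intervention.** The article states that "the occurrence and impact of possible negative effects during treatment will be measured using the 20-item Negative Effects Questionnaire" and that "a self-developed 24-item questionnaire on adverse effects commonly observed during CBT-I will be used". No difference between arms is stated. The section on retention {18b} says that all questionnaires are completed by online survey and that patients who stop treatment are still asked to complete the later assessments.

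**Events during treatment.** The article adds that "adverse events related to treatment (e.g. fatigue, sleepiness) will be assessed continuously during treatment". Collection then splits by arm:

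- Internet arm: "In the therapist-guided iCBT-I group, patients will be asked to report adverse events in sessions 2 through 6". The intervention description {11a} says where these sessions take place: "The therapist-guided iCBT-I will be delivered via an access-controlled online platform".
- Face-to-face arm: "During face-to-face CBT-I, therapists will ask for adverse events and record them in a designated electronic case report form (eCRF".

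The blinding section {17a} says that neither patients nor therapists can be blinded. The abstract's list of secondary outcomes includes "adverse events related to treatment, and a health-economic evaluation". The Discussion, under Study contributions, counts harms data gathered both after and throughout treatment among the trial's contributions, "thereby providing more data on the safety of therapist-guided iCBT-I".

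**The concern.** Reported event rates depend on who asks, how, how often and who writes the answer down. Here those features change with the arm. A patient entering an event in a web programme and a therapist asking in person and completing a form may capture different fractions of the same events.

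Three parts of the article make this matter:

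- The abstract treats adverse events as a secondary outcome, and the statistical methods section {20a} says that secondary endpoints are analysed much like the primary one, with treatment effects and 95% confidence intervals. Nothing in the article exempts the in-session events from such a comparison.
- The section on harms {22} says that the commonest effects are transient and occur early in treatment. The in-session stream is closest in time to them, so it is likely to be used.
- The data monitoring committee reviews adverse events {21a}. A collection artefact could look like a safety signal or hide one.

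Both routes also need an attended session. A patient who stops because of side effects leaves this stream at the moment when the information matters most.

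**Working it through.** The article gives no event rate or capture rate, so there is no plan figure to reproduce. The check is a comparison of the text, followed by an illustration on assumed inputs.

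**1. The two routes side by side**

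| Feature | Internet arm | Face-to-face arm |
|---|---|---|
| Who raises the question | Patient is asked within a web session | Therapist asks |
| Who reports or records | Patient reports | Therapist records in the eCRF |
| Sessions named | 2 to 6 (five occasions) | None named |
| Blinded to arm | No | No |
| Needs an attended session | Yes | Yes |

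The first three rows differ by arm. Every patient in an arm has that arm's route, so arm and route are the same variable in this stream. No covariate or model can separate them.

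**2. The questionnaires**

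The 20-item and 24-item instruments have the same time points, the same online mode and no stated arm difference. Patients who discontinue treatment are also asked to complete them. The confounding in step 1 does not arise.

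**3. Illustration of possible size (all rates assumed)**

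Inputs: n = 422/2 = 211 per arm, with no attrition; the same true risk r in both arms; capture of 90% in arm A and s in arm B; two-sided 5% test. Which arm captures more is left open.

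Observed proportions: pA = 0.9r and pB = s × r, with mean p̄.

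Chance of p < 0.05 ≈ Φ{ [ (pA − pB) − 1.96 √(2p̄(1 − p̄)/n) ] / √( [pA(1 − pA) + pB(1 − pB)]/n ) }

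Worked case, r = 0.40 and s = 0.60: pA = 0.36, pB = 0.24, p̄ = 0.30.

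- 1.96 × √(2 × 0.30 × 0.70/211) = 1.96 × 0.0446 = 0.0874
- √((0.2304 + 0.1824)/211) = 0.0442
- (0.12 − 0.0874)/0.0442 ≈ 0.74, and Φ ≈ 0.77

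Spurious difference in percentage points, with the chance of significance in brackets:

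| True risk in both arms | 90% v 80% | 90% v 70% | 90% v 60% |
|---|---|---|---|
| 20% | 2 (8%) | 4 (20%) | 6 (41%) |
| 40% | 4 (14%) | 8 (42%) | 12 (77%) |
| 60% | 6 (23%) | 12 (70%) | 18 (96%) |

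**4. Masking**

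With the same assumed rates, a true risk of 60% captured at 60% shows as 0.60 × 0.60 = 36%. A true risk of 40% captured at 90% shows as 0.40 × 0.90 = 36%. A real gap of 20 points would then disappear.

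**The case against.** The strongest reply is that the trial already has a common harms measure. The two questionnaires come first in the Safety section, the in-session events are an addition, and the 20-item instrument covers negative effects during treatment. That stands, and it limits the point to the in-session stream. A reader might infer that no between-arm statement on harms is possible, or that the trial cannot meet its safety aim. The documents do not support either. The questionnaires provide a comparison without this defect, although unblinded self-report remains a limit. The stated aim is only to add data on the safety of the internet treatment.

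It can also be said that no test of in-session events is announced, that the detailed list of secondary outcomes omits adverse events, and that the choice of harms source belongs in the statistical analysis plan, which is not shown. This is fair as to what will be analysed. It does not remove the problem, because the article itself fixes the collection rule. An analysis plan can only limit what is inferred from the data.

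Events are prompted in both arms, the same therapists treat both arms, and the question wording may match in Appendix 1, which is not shown. The contrast may therefore be milder than it looks, and the sessions used in the face-to-face arm may be named elsewhere. Matching wording would still leave the stated difference in who reports and who records.

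Finally, the capture rates are assumptions. That is correct: the table shows what could happen and is not an estimate.

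**Conclusion.** The point holds for adverse events collected during treatment, and only for those. In that stream the collection route is fully confounded with arm, and attendance determines who can contribute. A difference between arms could be produced by collection alone, and equal rates could hide a real difference.

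The size and direction are unknown. Under the assumed rates, the spurious gap runs from 2 to 18 points and the chance of nominal significance from 8% to 96%. These figures presuppose a significance test on in-session events, which the article neither describes nor rules out.

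The conclusion rests on the Safety section as written and on the web sessions being where internet-arm patients report. It does not affect the primary outcome or the questionnaire-based harms data. It is a cheap improvement worth making.

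**What to change.** 1. State that the between-arm harms comparison rests on the 20-item and 24-item questionnaires at post-intervention, for all randomised patients who complete them, including those who stopped treatment.
2. Report in-session adverse events descriptively by arm. State beside the figures how they were collected in each arm and how many sessions were attended. Give the data monitoring committee the same note.
3. Optionally, for patients still to be enrolled, send the same short online adverse-event form to both arms at the same weeks after randomisation, and analyse it only among those patients.

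Items 1 and 2 need only wording. Their drawback is that a questionnaire 10 weeks after randomisation relies on recall of early, transient effects. Item 3 would reduce that problem at the price of one more automated survey and a small burden on patients. Its value shrinks as enrolment proceeds: the article reports 106 of 422 patients enrolled by 26 February 2024, which already left at most 422 − 106 = 316, and expected recruitment to finish around December 2024. Data from the form could not be pooled with patients enrolled before it was introduced.
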